## Abstract

**Background:**

Cancer survivors treated with any dose of radiation to the abdomen, pelvis, spine, or total body irradiation (TBI) are at increased risk for developing colorectal cancer (CRC) compared to the general population. Since earlier detection of CRC is strongly associated with improved survival, the Children’s Oncology Group (COG) Long-Term Follow-Up Guidelines recommend that these high-risk cancer survivors begin CRC screening via a colonoscopy or a multitarget stool DNA test at the age of 30 years or 5 years following the radiation treatment (whichever occurs last). However, only 37% (95% CI 34.1–39.9%) of high-risk survivors adhere to CRC surveillance. The **A**ctivating cancer **S**urvivors and their **P**rimary care providers (PCP) to **I**ncrease colo**re**ctal cancer **S**creening (ASPIRES) study is designed to assess the efficacy of an intervention to increase the rate of CRC screening among high-risk cancer survivors through interactive, educational text-messages and resources provided to participants, and CRC screening resources provided to their PCPs.

**Methods:**

ASPIRES is a three-arm, hybrid type II effectiveness and implementation study designed to simultaneously evaluate the efficacy of an intervention and assess the implementation process among participants in the Childhood Cancer Survivor Study (CCSS), a North American longitudinal cohort of childhood cancer survivors. The Control (C) arm participants receive electronic resources, participants in Treatment arm 1 receive electronic resources as well as interactive text messages, and participants in Treatment arm 2 receive electronic educational resources, interactive text messages, and their PCP’s receive faxed materials. We describe our plan to collect quantitative (questionnaires, medical records, study logs, CCSS data) and qualitative (semi-structured interviews) intervention outcome data as well as quantitative (questionnaires) and qualitative (interviews) data on the implementation process.

**Discussion:**

There is a critical need to increase the rate of CRC screening among high-risk cancer survivors. This hybrid effectiveness-implementation study will evaluate the effectiveness and implementation of an mHealth intervention consisting of interactive text-messages, electronic tools, and primary care provider resources. Findings from this research will advance CRC prevention efforts by enhancing understanding of the effectiveness of an mHealth intervention and highlighting factors that determine the successful implementation of this intervention within the high-risk cancer survivor population.

**Trial registration:**

This protocol was registered at clinicaltrials.gov (identifier NCT05084833) on October 20, 2021.

**Supplementary Information:**

The online version contains supplementary material available at 10.1186/s12913-022-08082-3.

## Background

### Cancer survivors and CRC risk

With the tremendous success in the treatment of childhood and adolescent cancer, there is a growing population of over 500,000 childhood cancer survivors in the US [1]. However, childhood cancer survivors are at risk for morbidity and premature mortality associated with their primary cancer and its treatment, with a 10.4 year loss of life expected compared to the general population [2–5]. While recurrence of the primary disease is the leading cause of premature mortality, subsequent malignant neoplasms (SMN) are the second leading cause among childhood cancer survivors. Focused efforts for early identification and prevention of these SMNs are needed to reduce mortality in this population.

A standardized incidence ratio (SIR), the ratio of the observed number of cases in a cohort compared to the expected number in the age-matched general population, indicates that childhood cancer survivors treated with abdominal or pelvic radiotherapy (RT) are almost four times (SIR 4.2, 95% CI 2.8–6.3) more likely to develop CRC compared to the general population, with their elevated risk evident by the age of 30 years with no plateau [6]. In fact, CRC represents the greatest absolute excess risk (AER) of all digestive subsequent primary neoplasms (SPNs) in childhood cancer survivors, with 11 excess colorectal cancers per 100,000 person-years (95% CI: 9–13) [7]. As in the general population, childhood cancer survivors usually develop screen-detectable adenomas prior to the development of a carcinoma [8, 9]. Since earlier detection of precancerous lesions (i.e., adenomas) is strongly associated with improved survival in the general population, screening with colonoscopy or a multitarget stool DNA test is recommended by the Children’s Oncology Group Long-Term Follow-Up Guidelines [10, 11] starting at age 30 years or 5 years following RT (whichever occurs last) in all survivors exposed to any dose of RT to the abdomen, pelvis, spine, or total body irradiation (TBI).

Prior work has shown that most survivors are unaware of: 1) their risk for SMN, including CRC; and 2) their recommended screening [12]. The majority of adult survivors of childhood cancer are no longer followed at a cancer center, and most primary care physicians (PCP) who care for survivors are similarly unaware of the risks or guidelines for CRC screening [13, 14]. Consequently, many survivors at elevated risk for CRC are not screened according to current recommendations, placing them at risk for preventable morbidity and premature mortality. Indeed, only 37% (95% CI 34.1–39.9%) of high-risk survivors adhere to CRC surveillance [15].

### Present study

This article describes a hybrid type II effectiveness and implementation study, entitled, “**A**ctivating cancer **S**urvivors and their **P**rimary care providers (PCP) to **I**ncrease colo**re**ctal cancer **S**creening” (ASPIRES). The intervention trial will simultaneously focus upon the effectiveness of an mHealth intervention for participant CRC screening completion (colonoscopy, negative multitarget stool DNA test, or positive multitarget stool DNA test + colonoscopy) and the evaluation of the implementation process using the Consolidated Framework for Implementation Research (CFIR) [16]. This article highlights the intervention design and study procedures related to conducting a hybrid effectiveness-implementation study targeting childhood cancer survivors.

To accomplish the study objectives, the project will utilize the infrastructure of the Childhood Cancer Survivor Study (CCSS), a 31-institution retrospective cohort that includes 25,655 5-year survivors of childhood cancer diagnosed and treated in the United States and Canada between 1970 and 1999. The CCSS Coordinating Center, located at St. Jude Children’s Research Hospital, is a pivotal partner in this project [17].

### Conceptual framework

The ASPIRES study is guided by the Patient Activation Model [18], which suggests that activated patients are better prepared to participate in self-management. Patient activation is the degree to which an individual understands they must play an active role in managing their own health and health care, and the extent to which they feel able to fulfill that role [19]. Individuals with higher levels of patient activation are more likely to undergo screening [20]. Activation involves four stages: (1) believing that taking an active role as a patient is important; (2) having the confidence and knowledge necessary to take action; (3) taking action to maintain and improve one’s health; and (4) staying the course even under stress [18].

Although the Patient Activation Model is a vital component of our conceptual model, we will include other important variables, many of which are from the Health Belief Model [21, 22] and the Transtheoretical Model [23–27]. These variables include benefits and barriers to screening; implementation intentions; perceived seriousness of susceptibility to CRC; and self-efficacy.

The ASPIRES study is enhanced by direct health care provider activation. PCP activation is designed to increase provider knowledge about the high-risk status of childhood cancer survivors and national screening recommendations, improve the motivation to discuss with, and order testing for, their patients, and facilitate effective information exchange and communication [28, 29]. We will examine specific factors (i.e., years in practice, location, knowledge) that may impact PCP activation.

### Objectives

The ASPIRES study will assess the effectiveness, cost-effectiveness, and implementation of an intervention to increase the rate of CRC screening (colonoscopy and/or multitarget stool DNA test) among high-risk cancer survivors through interactive, educational text-messages and electronic resources provided to participants, and CRC screening resources provided to their primary care providers. The study objectives are listed below:

#### Primary objective

Evaluate the difference in the proportion of patients who complete the colonoscopy or multitarget stool DNA test (multitarget stool DNA test plus colonoscopy if multitarget stool DNA test is positive) within 12 months of enrolling on this study; this will be measured via self-report questions in the patient questionnaire.

#### Secondary objectives

Evaluate the difference in the proportion of patients who complete the colonoscopy or multitarget stool DNA test (multitarget stool DNA test plus colonoscopy if multitarget stool DNA test is positive) within 12 months of enrolling on this study; this will be measured via medical record confirmation.Explore differences in the rates of completion of the colonoscopy or multitarget stool DNA test (multitarget stool DNA test plus colonoscopy if multitarget stool DNA test is positive) between the two intervention arms.Use the CFIR to evaluate the implementation process and identify potential barriers and facilitators to the uptake of the intervention.Identify potential moderators and mediators of the uptake of CRC screening that may strengthen or weaken the effectiveness of the proposed intervention.Estimate the costs and incremental cost-effectiveness of the proposed intervention.

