### Data analysis plan

#### Primary efficacy analysis

The primary analysis involves comparing the proportion of participants who report obtaining a colonoscopy or negative multitarget stool DNA test report or positive multitarget stool DNA test report in combination with a confirmed colonoscopy (completed screening test) in each intervention arm to the control arm. To account for the randomization strata and the sampling scheme, this difference will be estimated by taking a weighted average of the differences in stratum-specific proportions. The test of the difference in proportions will be done using a Cochrane-Mantel-Haenszel test [40].

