### Sample size and power

The primary aim involves two pair-wise comparisons of equal importance. We fix the probability of a Type I error at 0.025 for each comparison in order to maintain the overall probability of a Type I error at 0.05. We powered the study to detect a difference of 20% for each pair-wise comparison, assuming equal randomization to each of the three arms, and that approximately 20% of participants in the control arm will be adherent with recommended CRC screening. Table 5 shows the power we expect to have using two-sided Cochrane-Mantel-Haenszel tests and indicates that we should have sufficient power to detect a clinically meaningful difference even if the proportion of participants in the control arm with the primary endpoint is somewhat different than we expect.

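### The randomized contrast that isolates PCP activation (C+PA+PCP v C+PA) is left exploratory, although it could be tested formally behind the primary tests at no alpha cost

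*Protocol article*

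**What the plan says.** The arms are nested (protocol article, Study design). Control receives electronic resources, C+PA adds interactive text messages, and C+PA+PCP adds educational materials faxed to the participant's PCP.

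The Primary efficacy analysis compares the proportion screened "in each intervention arm to the control arm". Sample size and power states: "The primary aim involves two pair-wise comparisons of equal importance". The level of each test is given next: "We fix the probability of a Type I error at 0.025 for each comparison". Together the two tests use up the stated overall level of 0.05. The stated sizing is also for these comparisons: "We powered the study to detect a difference of 20% for each pair-wise comparison".

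The comparison of the two intervention arms appears only under Secondary objectives, as "Explore differences in the rates of completion of the colonoscopy or multitarget stool DNA test". The text gives it no alpha, no place in a testing order and no power. Provider activation is nevertheless presented as a distinct component in the Conceptual framework: "The ASPIRES study is enhanced by direct health care provider activation". The cost-effectiveness analysis compares all three arms on cost per additional person screened.

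**The concern.** C+PA+PCP v C tests the whole package of texts and PCP materials. It can be positive because of the texts alone, so it says nothing about what the PCP materials add. Only C+PA+PCP v C+PA does that, and the plan gives this contrast no error control.

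At stake is the kind of statement the trial can make about the component that sets the third arm apart. A positive result against control could be credited to the fax by a reader, while a difference between the intervention arms could be reported only as exploratory. A three-arm design does not force this limit. The contrast can be given formal status without taking anything from the primary tests.

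**Working it through.** **Inputs from the protocol article.** 315 participants (Eligibility) and equal randomization give 315 / 3 = 105 per arm. Control rate is about 20%, the target difference is 20 points, and alpha is two-sided 0.025 per primary comparison (Sample size and power).

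**Assumptions.** The article gives no rate for C+PA beyond the 20-point target and no increment for PCP activation. I take C+PA at 40% (20% + 20 points) and increments of 5 to 20 points. No loss to follow-up is assumed for the main figures, with a 20% loss (84 per arm) as sensitivity. An unstratified pooled z test stands in for the planned stratified test.

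**1. The plan's own figure.** 0.025 + 0.025 = 0.05, as stated. All of the alpha is used by the two control comparisons. The power table is not shown, so its entries cannot be compared. The formula used is power = Φ[(d − z·s0)/s1], with s0 = √(2p̄(1−p̄)/n) and s1 = √((p1(1−p1)+p2(1−p2))/n).
- For 20% v 40% at 0.025: s0 = √(2×0.3×0.7/105) = 0.0632, s1 = √((0.16+0.24)/105) = 0.0617, z = 2.241.
- Power = Φ[(0.20 − 0.1418)/0.0617] = Φ(0.944) = 82.7%.

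**2. Why the gate controls error.** Write H1: C+PA = C, H2: C+PA+PCP = C, H3: C+PA+PCP = C+PA. Any two of these imply the third, so either all three are true or at most one is. The rule tests H1 and H2 at 0.025 each, and tests H3 at 0.05 only if H1 or H2 is rejected.
- All three true: no error can occur unless H1 or H2 is rejected, so the error is at most 0.025 + 0.025 = 0.05.
- Only H3 true: the error is at most 0.05.
- Only H1 or only H2 true: the error is at most 0.025.

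**3. Simulation (400,000 trials per scenario, 105 per arm).**

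| C / C+PA / C+PA+PCP (%) | Family-wise error |
|---|---|
| 20/20/20 | 0.047 |
| 20/40/40 | 0.051 |
| 20/20/40 | 0.025 |

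The 0.051 reflects the discreteness of the z test, which by itself rejects a true H3 at 0.051 there. Without the gate, adding a 0.05 test to the two primary tests gives 0.086 at 20/20/20, so the gate is essential.

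**4. What the package comparison shows.** At 20/40/40, where PCP activation adds nothing, C+PA+PCP v C is still significant at 0.025 in 83% of trials. That is a correct result for the package.

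**5. Power of C+PA+PCP v C+PA at two-sided 0.05, 105 per arm.** Example, 40% v 50%: s0 = √(2×0.45×0.55/105) = 0.0687, s1 = √((0.24+0.25)/105) = 0.0683, so power = Φ[(0.10 − 1.96×0.0687)/0.0683] = Φ(−0.51) = 31%.

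| Increment over 40% | Before gating (formula) | After gating (simulated, control 20%) |
|---|---|---|
| 5 points | 11% | 11% |
| 10 points | 31% | 30% |
| 15 points | 59% | 57% |
| 20 points | 83% | 82% |

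The gate costs almost nothing here, because it opens in at least 97% of trials in these four scenarios. If C+PA is at 30%, a 10-point increment has 33% power before gating and 32% after. With 84 per arm, 40% v 50% has about 25% by formula and 26% after gating by simulation. Reaching 80% power would need 388 per arm for 10 points and 173 per arm for 15.

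**6. Precision.** At 40% v 40%, the 95% CI half-width is 1.96 × √(2×0.24/105) = 0.133, or about 13 points.

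**The case against.** The strongest reply is that nothing here is wrong. The objectives, the primary analysis and the sample size section agree with one another, and ranking this contrast as exploratory is stated openly. That stands, and the point is offered as an improvement only.

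A reader might go further and infer that the trial cannot conclude anything about what PCP activation adds. The documents do not support that. The contrast is a listed, randomized secondary objective, and it yields an estimate and a confidence interval under either label. What is missing is an error-controlled claim.

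A reader might also infer that the plan will credit the fax for a positive C+PA+PCP v C result. No section says so. The overall objective describes a package of texts, electronic resources and PCP resources, and the comparison with control answers that question properly.

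It can also be said that power is the real limit, and for increments of 15 points or less this is right. Some participants may also have no PCP to receive materials (Study design), which would dilute the contrast further. This is a reason to state the power, not to withhold a test that costs nothing.

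Finally, an analysis plan that is not shown may place the contrast in a testing order. That is possible. The point does not rest on silence, however: the article itself labels the contrast exploratory and assigns the full alpha elsewhere.

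**Conclusion.** The point holds as a free improvement, not as an error or contradiction. As written, the trial can estimate the added effect of PCP activation, to about ±13 points, but cannot make an error-controlled claim about it. Gating on at least one significant primary comparison removes that limit, with family-wise error at a nominal 0.05 and both primary tests untouched.

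The gain depends on the true increment. The chance of a formal positive finding goes from none to about 30% for 10 points, 57% for 15 and 82% for 20. These figures rest on 105 evaluable per arm, 20% screened in control and an assumed 40% in C+PA, and attrition lowers them. The error-control argument does not depend on the assumed rates, provided each test holds its own level. For smaller increments a non-significant result is the likely outcome, and it would not show that PCP activation adds nothing.

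**What to change.** In Secondary objectives, Primary efficacy analysis, and Sample size and power:

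- Keep both primary comparisons at two-sided 0.025.
- Add that, if at least one of them is significant, C+PA+PCP v C+PA will be tested at two-sided 0.05 with the same stratified test.
- Report the estimate and 95% CI for this contrast whether or not the gate opens.
- Say that statements about the added value of PCP activation will rest on this contrast.
- State its power with the assumptions (about 11%, 31%, 59% and 83% for 5, 10, 15 and 20 points over 40%, with 105 per arm and no losses, and lower with attrition), and that a non-significant result will not be read as evidence of no added effect.

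The cost is wording in the protocol and analysis plan, settled before outcome data are seen by arm. No alpha, participants or data collection are needed. The one consequence is having to say openly that power is low for modest increments.

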## Methods

### Study design

We will use a hybrid type II effectiveness and implementation design [30], to study the intervention’s effectiveness while also identifying facilitators and barriers to the implementation of the intervention [31]. While the University of Chicago will manage the study, our partners will play key roles. Memorial Sloan Kettering Cancer Center collaborators will conduct much of the data analysis, Columbia University colleagues will lead the cost and cost-effectiveness analysis, and the CCSS Coordinating Center partners at St. Jude Children’s Research Hospital will lead participant recruitment, administer the electronic informed consent process (see Additional File 1), create a study website for participants within their previously established personal study portal, and implement a messaging plan to communicate key study components to participants.

Participants will be randomized to one of three arms; the Best Practices Control (C) arm receives electronic educational resources (see Additional File 2) via the study website, the C + Patient Activation (PA) arm receives electronic educational resources via the study website as well as interactive text messages with links to videos and resources, and the C + PA + PCP Activation arm receives electronic educational resources via the study website, interactive text messages with links to videos and resources, and their PCPs are faxed educational materials (Fig. 1). For the purposes of this study, a PCP refers to a primary care provider or some other health care provider who the survivor sees regularly for care and who can order health screenings. Randomization will be stratified by age at study enrollment (30–44 and ≥ 45 years). We will use a permuted block randomization scheme with a random block size ranging from 6 to 12. The study principal investigators will be blinded to arm assignment.

**Fig. 1 Fig1:**
[figure not shown]
ASPIRES STUDY flow diagram

Participants will be in the study for up to 15 months. All participants will complete a baseline and 12-month questionnaire via the CCSS Long-Term Follow Up study website (“My LTFU”). After completion of each of these questionanires, a participant will receive a $50 Amazon giftcard. A sample of 20 participants from each intervention arm will be invited to take part in an interview within 3 months after the completion of the 12-month questionnaire (see Implementation Outcome section below for more details). These interviewees will each receive a $50 Amazon giftcard. The primary care provider of each participant will complete a faxed baseline and 12-month questionnaire which include items to measure PCP activation, demographics, experience and comfort level providing care to cancer survivors, and knowledge about the healthcare needs of childhood cancer survivors; the 12-month questionnaire also includes CFIR items to aid in the evaluation of the implementation process. The PCPs will receive a $25 Amazon giftcard for completion of the baseline questionnaire, and a $50 Amazon giftcard for completion of the 12-month questionnaire. To gather additional data regarding the implementation process, we will also ask one medical office staff member associated with each participant’s PCP to complete a 12-month questionnaire via the phone. The medical office staff members will each receive a $25 Amazon giftcard for completion of the questionnaire. A sample of 20 primary care providers and 20 medial office staff from each intervention arm will take part in an interview within 3 months after the completion of the12-month questionnaire. Each interviewee will receive a $50 Amazon giftcard. We will identify each participant’s primary care provider by including a required section on the baseline questionnaire for participants to provide their PCP’s name and contact information. Similarly, the contact information for one medical office staff member working with each PCP will be collected via the baseline survey completed by each PCP. Participants without a PCP will be provided with a resource to encourage them to find a PCP, and will be asked repeatedly throughout the study to provide the study team with contact information for their PCP if one has been identified. The current study was approved by the University of Chicago Institutional Review Board (IRB20–1247), St. Jude Children’s Research Hospital Institutional Review Board (IRB21–0901), Memorial Sloan Kettering Cancer Center Institutional Review Board (IRB21–446), and the Columbia University Institutional Review Board (IRB-AAAT9278).
